## Methods

The overarching goal of this research is to compare and contrast the nature of cancer genetic counseling encounters and patient-centered outcomes between Black and White patients in the naturalistic clinical setting. We will test our hypotheses by addressing four specific aims: **Aim 1**) To compare/contrast the nature of patient-provider communication by patient race (Black vs. White); **Aim 2**) To compare/contrast the clinical discussion content by patient race; **Aim 3**) To quantify the role of each type of counselor bias in patient-provider communication (Aim 1) and clinical discussion content (Aim 2); and **Aim 4)** To quantify the role of patient-provider communication and clinical discussion content with patient-centered outcomes (trust, satisfaction, therapeutic alliance, empowerment, genetic testing completion). These aims will be achieved through an observational study with a convergent mixed methods research design. Table 1 provides an overview of the study design.

**Table 1 Tab1:** An overview of the study designs

Aims	Data sources	Analyses	Goals
1	• Recorded encounters	Quantitative analyses of provider communication style and the overall quality of patient-provider communication Qualitative analyses of transcribed encounters for the four basic interaction structures	Identify specific aspects of patient-provider communication during cancer genetic counseling encounters that are different between Black and White patients
2	• Recorded encounters	Qualitative analyses of transcribed encounters for (1) the presence/absence of the key topics for risk communication and genetic test consent during cancer genetic counseling encounters that were identified by NCI; and (2) additional topics discussed during cancer genetic counseling encounters	Identify specific clinical discussion topics during cancer genetic counseling encounters that are different between Black and White patients
3	• Provider baseline survey • Patient baseline survey • Coded encounters	Quantitative analyses of associations between the four forms of provider bias and (1) patient-provider communication as well as (2) clinical discussion content that were identified in Aims 1 & 2	Identify specific aspects of patient-provider communication/clinical discussion topics that contribute to racial disparities in the cancer genetic counseling process and reflect provider bias

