To assess *the linguistic patterns of* patient-provider communication, we will both observe recordings and analyze transcripts. Specifically, we will examine genetic counseling providers’ linguistic patterns that reflect constructs associated with levels of implicit prejudice during racially discordant interactions in prior research, including social dominance, [52, 53] intergroup anxiety, [54–56] and avoidance (or lack of engagement) [57–59]. For social dominance, we will code: [1] patient-provider talk time ratio [25, 60]; [2] frequency of first person plural pronouns [26]; [3] turn-taking ratio [61, 62]; and [4] the number of interruptions and overlapping speech [63, 64]. For intergroup anxiety, we will code: [1] frequency of anxiety-related words (e.g., worried, afraid, nervous); [26] and [2] frequency of hesitation markers (e.g., uh, uhm, umm). For avoidance, we will code: [1] encounter length; and [2] frequency of back-channeling responses (e.g., Okay, yes, ah huh) [65].

Frequencies (i.e., first person plural pronouns, anxiety-related words, hesitation markers, back-channeling responses) will be assessed with the Linguistic Inquiry and Word Count (LIWC) software [66]. Each recording will be first transcribed verbatim, and then the verbatim transcripts will be further edited using the guidelines specifically developed for text analysis using LIWC [67]. Finally, the edited transcripts will be divided into two documents: patient vs. provider speech. The LIWC computes the percentage of use of words in more than 70 + word categories; it also enables researchers to create new word categories. For the current analyses, we will use both existing (i.e., pronouns, affective processes) and new (i.e., hesitation markers, back-channeling responses) categories.

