The remaining coding will be conducted manually in steps. First, we will develop a linguistic codebook, which provides coding procedures, coding rules, descriptions, and examples of each linguistic pattern. Next, two senior research personnel will code a few transcripts and refine the linguistic codebook, and train two coders to apply the codes. The coders will then code all transcripts independently, while we check interrater reliability every 10 transcripts to prevent coder drift [68]. We will use the thresholds of *ICC* = 0.80 on 95% of codes [69]. We will use NVivo software to catalog and sort the coded data. Finally, we will take the findings from the analysis of linguistic patterns and create quantifiable units (Table 3) to be used in the statistical analysis.

**Table 3 Tab3:** An overview of the variables, measurements units, and regression types

Constructs and corresponding linguistic patterns		Units of measurement	Regression type

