**(1) Social dominance**			
	Patient-provider talk time	Duration	Linear
	First person plural pronouns	Proportion	Linear
	Turn-taking	Frequency	Poisson
	Interruptions and overlapping speech	Frequency	Poisson

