Aim 3 (to quantify the role of each type of counselor bias in patient-provider communication and clinical discussion content) examines Paths C and D in our conceptual model. Analyses will be carried out in three steps. In Step 1, we identify covariates associated with patient-provider communication or clinical discussion content. We will compute correlations among all facets of patient-provider communication/clinical discussion topics identified in Aims 1 & 2 and factors assessed in the baseline surveys (e.g., provider/patient demographics, provider professional characteristics, patient perceived discrimination). In Step 2, we compute partial correlations between all forms of provider bias and aspects of patient-provider communication/clinical discussion topics identified in Aims 1 & 2, controlling for covariates that were significantly associated with any of the provider behaviors. In Step 3, we conduct two regressions for each of the specific aspects of patient-provider communication and clinical discussion topics that remain statistically significant in Step 2. One regression will focus on the role of provider prejudice and will consist of four main effects (patient race, provider implicit prejudice, provider explicit prejudice, care modality), all six combinations of two-way interactions, all four combinations of three-way interactions, and one four-way interaction among all predictors. The second regression model will focus on the role of provider stereotyping and will consist of four main effects (patient race, provider implicit stereotyping, provider explicit stereotyping, care modality), all six combinations of two-way interactions, four combinations of three-way interactions, and one four-way interaction among all predictors. The type of each outcome, summarized in Table 4, will determine the regression model to analyze. The regressions will also include the same set of covariates as in Step 2. All four types of provider bias will be grand-mean-centered. We will use GEE and the Bonferroni corrections in analyses. The provider communication styles that remain statistically significant in Step 3 are considered as key communication styles that contribute to racial disparities in the cancer genetic counseling process and reflect provider bias.

**Table 4 Tab4:** An overview of the outcomes and analyses for each aspect of patient-provider communication and clinical discussion content

Outcome types	Variables	Analytical approaches

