Continuous: Likert scale	*Patient-provider communication* (Provider communication style; The overall quality of patient-provider communication)	Linear regression with GEE
Continuous: Frequency	*Patient-provider communication* (Each type of silence; Each type of adjacency pairs; Each type of problems)	Poisson regression with GEE
Continuous: Proportion	*Patient-provider communication* (Topics initiated by providers; Primary units allocated to providers; Silence followed by provider talks; Repairs initiated by providers; Problems repaired by providers)	Linear regression with GEE
Continuous: Duration	*Patient-provider commu*nication (Each type of silence) *Clinical discussion con*tent (The amount of time spent on discussing a given topic)	Linear regression with GEE
Dichotomy	*Clinical discussion content* (The presence/absence of a given discussion topic)	Logistic regression with GEE
Multiple categories	*Patient-provider communication* (The primary units of turns)	Multinomial logistic regression with GEE

Finally, Aim 4 (to quantify the impact of patient-provider communication/clinical discussion content with patient-centered outcomes) examines Paths E and F in our conceptual model. The analyses will be carried out in steps similar to those in Aim 3. In Step 1, we will identify covariates associated with patient-centered outcomes by computing correlations among all aspects of patient-provider communication/clinical discussion topics and factors assessed in the patient baseline survey, the provider baseline survey, and the provider post-encounter survey. In Step 2, we will compute partial correlations between all aspects of patient-provider communication/clinical discussion topics identified in Aims 1 and 2 and patient-centered outcomes while controlling for covariates identified in Step 1. In Step 3, we will conduct a linear regression with GEE and Bonferroni correction for each self-reported outcome (e.g., trust, satisfaction, therapeutic alliance) and a logistic regression with GEE for behavioral outcome (genetic testing completion). All regressions will include the same set of predictors (aspects of patient-provider communication/clinical discussion topics that remain significant in Step 2, and care modality) and covariates. Aspects of patient-provider communication/clinical discussion topics that remain significant in Step 3 are considered as potentially important intervention points for reducing racial disparities in patient-centered outcomes.

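### Table 4's linguistic outcomes do not match the eight that are coded, and Table 3 analyses talk time and turn-taking as raw amounts although the text defines them as ratios

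*Protocol article*

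**What the plan says.** **Coded outcomes.** The section on patient-provider communication quality defines eight linguistic outcomes: talk time, first-person plural pronouns, turn-taking, interruptions and overlaps, anxiety words, hesitation markers, encounter length and back-channeling. Talk time is a "patient-provider talk time ratio" and turn-taking is also called a ratio. Interruptions are a number. Encounter length is an avoidance measure in its own right.

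**Analysed units.** The same section says the linguistic findings will be used to "create quantifiable units (Table 3) to be used in the statistical analysis". Table 3 lists the same eight outcomes, with talk time as duration (linear), turn-taking as frequency (Poisson) and "Interruptions and overlapping speech" as frequency (Poisson).

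**Aim 3 models.** Under Statistical analysis, "The type of each outcome, summarized in Table 4, will determine the regression model to analyze". The linguistic entries of Table 4 are:
- frequency: "Each type of silence; Each type of adjacency pairs; Each type of problems"
- proportion: topic initiation and primary units by provider, and "Silence followed by provider talks; Repairs initiated by providers; Problems repaired by providers"
- duration: types of silence
- multiple categories: "The primary units of turns"

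**Only related text elsewhere.** The Aim 1 row of Table 1 announces "Qualitative analyses of transcribed encounters for the four basic interaction structures". The four structures are neither named nor defined.

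**Covariates.** For Aims 1 and 3, covariates are chosen by correlating the outcomes with factors from the baseline surveys. Care modality is in every model. No offset or exposure term is mentioned.

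**The concern.** There are two separate problems.

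First, the table said to govern Aim 3 names linguistic variables that no described coding step produces, and leaves out every linguistic variable that is coded. A reader cannot tell which set will be tested. The number of outcomes also matters to the Bonferroni correction planned for Aims 1 and 3. Aim 4 inherits the ambiguity because its predictors are the aspects identified in Aims 1 and 2.

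Second, a talk-time or turn-taking ratio does not grow with the length of the visit, but a raw duration or count does. Following Table 3, three of the four social-dominance measures would scale with encounter length, which the study itself treats as a possible sign of avoidance. The fourth, pronouns, is a proportion and already normalised, so one construct would mix normalised and unnormalised measures. A difference in visit length could then be read as a difference in dominance, or could cancel a real one.

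**Working it through.** **1. The lists side by side**

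| Outcome | Coding text | Table 3 | Table 4 |
|---|---|---|---|
| Talk time | ratio | duration, linear | absent |
| Turn-taking | ratio | frequency, Poisson | absent |
| Interruptions/overlaps | number | frequency, Poisson | absent |
| Pronouns, anxiety words, hesitation markers, back-channeling | percentage of words | proportion, linear | absent |
| Encounter length | length | duration, linear | absent |
| Silence, adjacency pairs, problems, repairs, topic initiation, turn units | not coded | absent | listed |
| Communication ratings; topic time; topic presence | coded | not linguistic | listed |

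None of the eight appears in Table 4. The ratio-versus-raw conflict affects exactly two variables, talk time and turn-taking.

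**2. Does each coded outcome still have a model?** Table 4 maps frequency to Poisson, and proportion and duration to linear. Table 3 uses the same mapping for all eight, so the model type is determinate.

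**3. Can encounter length enter the models?** It is measured from the recording, not in a baseline survey, so the stated covariate rule does not make it a candidate. Care modality does not remove a length difference between races within a modality.

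**4. Size of the length effect.** With the same rate per minute in both groups, expected count = rate × length, so

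apparent count ratio = (rate × length in Black patients) / (rate × length in White patients) = length ratio.

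Encounters 10% shorter give 0.90, and 20% shorter give 0.80. Conversely, a true interruption rate 1/0.90 = 1.11 (or 1/0.80 = 1.25) times higher would yield a count ratio of 1.00 and vanish.

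**5. How often would this be declared significant?** The article gives no figure to reproduce, so this is an illustration by simulation.
- From the article: 15 providers, 220 patients, near-equal race split within provider, GEE.
- Assumed: mean length 50 minutes, log-SD of length 0.3, 0.5 events per minute (25 per visit), gamma overdispersion 0.05, provider log-SD 0.15, provider talk share 0.6 with log-SD 0.1.
- Model: race only, exchangeable correlation, bias-reduced standard errors, t with 13 df, 300 runs per row.
- True rates and true talk shares are equal by race throughout. The Bonferroni level 0.05/8 = 0.00625 is an assumption based on the eight outcomes of Table 3.

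| Length difference | Count ratio, no offset | Rejection at 0.05 | Rejection at 0.05/8 | With log-length offset, at 0.05 | Raw talk time, at 0.05 | Raw talk time, at 0.05/8 | Talk share, at 0.05 |
|---|---|---|---|---|---|---|---|
| 0 | 1.00 | 5% | 0% | 4% | 3% | 0% | 4% |
| -5% | 0.95 | 11% | 2% | 5% | 15% | 3% | 4% |
| -10% | 0.90 | 35% | 10% | 6% | 56% | 20% | 2% |
| -15% | 0.85 | 71% | 34% | 4% | 93% | 69% | 3% |
| -20% | 0.80 | 93% | 64% | 5% | 99% | 94% | 4% |

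The talk-time difference follows the same logic. At -10% it should be 0.6 × 50 × 0.10 = 3.0 minutes, and the simulation gave 2.9. With the offset, the estimated rate ratio stayed between 0.995 and 1.001. Monte Carlo error is about √(0.35 × 0.65/300) ≈ 3 percentage points in the middle of the range.

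**The case against.** A reader might infer that Aim 3 cannot be run. The documents do not support that. Aim 3 ties the model to the type of outcome, Tables 3 and 4 agree on the mapping, and the rating, topic-time and topic-presence rows of Table 4 refer to coded data. What remains is an irreconcilable variable list.

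A missing offset is a detail an article may leave to its analysis plan, and for interruptions, a count in both places, it is the whole complaint. That is fair, and the offset alone would not be a finding. But for talk time and turn-taking the article gives two incompatible definitions and says that Table 3's units are the ones analysed. The covariate rule then closes the obvious route to adjustment.

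A reader might also infer that shorter visits with Black patients would produce a false signal of greater dominance. The direction is the reverse: fewer turns and interruptions would look like less dominance, against the study's hypothesis, and could mask a higher rate. Nor does the article say that length differs by race. Length is tested separately, so a difference would be visible when the counts are interpreted, although the count models would not adjust for it.

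Finally, Table 1 mentions interaction structures, so Table 4 may reflect a planned analysis that the article under-describes. This stands: the documents do not show which list is intended.

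**Conclusion.** The point holds on two internal contradictions. Table 4's linguistic variables match neither the coding section nor Table 3, and talk time and turn-taking are ratios in the text but raw amounts in Table 3. It should be corrected, but it does not invalidate the study.

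The statistical consequence is conditional: it arises only if encounter length differs by patient race or provider bias. The identity between count ratio and length ratio needs only equal rates per minute. The rejection percentages rest on the assumed length, rate and variability, and on a model without modality or covariates. A 5% length difference matters little once Bonferroni is applied (2% for counts, 3% for talk time). At 20% it dominates the result (64% and 94%). The figures at 0.05/8 are the nearer guide to the planned analysis, but the family size is itself an assumption.

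**What to change.** 1. Reconcile Table 4, and the four interaction structures in Table 1, with the coding section and Table 3. Either list the eight coded outcomes in Table 4, or define the other structures and describe how they will be coded.
2. Analyse talk time and turn-taking as the ratios the text defines (for example, provider share or log ratio), and change their unit and regression type in Table 3 to match.
3. Add log(encounter length) or log(total words) as an offset in the Poisson GEE for interruptions.
4. Keep encounter length as its own avoidance outcome.

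If the eight outcomes are kept, the cost is corrected tables and one offset from a variable already recorded. Retaining the extra structures would need a codebook and additional coding.

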#### General trust in genetic counselors

We will assess patients’ expectation about their trust in general counselors within the specific health system with a modified version of the Wake Forest Physician Trust Scale, which has been found to have better internal consistency (*α* = 0.93, test-retest reliability = 0.75), validity, discriminability, and scale distribution as compared to other trust scales [82, 83]. To account for patients having never met with a genetic counselor, they will be instructed to indicate how they expect to feel regarding trust in their counselor. The response items will range from 1 (Strongly disagree) to 5 (Strongly agree).

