#### Provider-specific trust

We will assess patient trust in the specific genetic counseling provider they have just met with a modified version of the Wake Forest Physician Trust Scale [83]. Items will be modified to reflect the specific provider a patient saw during their encounter.

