#### Perceived empowerment

We will use the same GOS [85] as in the patient baseline survey to assess perceived empowerment.

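### The Aim 4 covariate screen leaves out the outcomes it is meant to screen against, so the baseline empowerment and trust scores enter their models only if they correlate with a communication or discussion aspect

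*Protocol article*

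**What the plan says.** The Methods section names five "patient-centered outcomes (trust, satisfaction, therapeutic alliance, empowerment, genetic testing completion") for Aim 4. The Aim 4 paragraph of the Statistical analysis section then sets out three steps.

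- **Step 1** is to "identify covariates associated with patient-centered outcomes by computing correlations among all aspects of patient-provider communication/clinical discussion topics and factors assessed in the patient baseline survey". Two provider surveys, one at baseline and one after each encounter, complete the list. The patient post-encounter survey and the chart outcome are not listed.
- **Step 2** computes partial correlations between aspects and outcomes "while controlling for covariates identified in Step 1".
- **Step 3** fits one linear GEE model per self-reported outcome and a logistic GEE for testing completion. All models share the same right-hand side: the aspects "that remain significant in Step 2, and care modality) and covariates". No change score is defined and no baseline score is required.

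Two of the five outcomes have a baseline counterpart on the same instrument. For empowerment, the post-encounter survey section states: "We will use the same GOS [85] as in the patient baseline survey to assess perceived empowerment". Trust is measured at both times "with a modified version of the Wake Forest Physician Trust Scale"; at baseline patients are asked about expected trust ("they will be instructed to indicate how they expect to feel regarding trust in their counselor"), and afterwards the items refer to the provider they saw.

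**The concern.** A step whose purpose is to find covariates for an outcome has to look at that outcome. Step 1 looks at the predictors instead. The likely origin is Aim 3, whose Step 1 also correlates communication and discussion aspects with survey factors. That is correct there, because those aspects are the Aim 3 outcomes. Aim 4 follows similar steps with different outcomes, but the correlated pair was not changed.

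The consequence is clearest for the scores taken twice. A patient's baseline empowerment or expected trust is an obvious candidate predictor of the same score after the encounter, and the Data collection section says the baseline survey was designed to supply covariates of this kind. Under the written steps, such a score is retained because of its correlation with provider behavior, however well or badly it predicts the outcome. Aspects that survive Step 3 are to be treated as potential intervention points, so avoidable imprecision at this stage matters.

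**Working it through.** The article states no power or precision figure for Aim 4. Its only power statement concerns implicit prejudice and communication style, so there is no figure to reproduce for this point.

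**1. What Step 1 correlates**

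| | Stated purpose | Stated computation |
|---|---|---|
| One side | candidate covariates | factors from three surveys (patient baseline, provider baseline, provider post-encounter) |
| Other side | patient-centered outcomes | communication and discussion aspects |

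Step 2 brings in the outcomes, but by then the covariate set is fixed.

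**2. Which outcomes have a baseline**

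| Outcome | Baseline | After |
|---|---|---|
| Empowerment | GOS | GOS |
| Trust | Wake Forest, expected trust | Wake Forest, provider seen |
| Satisfaction | PSQ-III, healthcare system | GCSS, provider and session |
| Alliance (patient-rated) | none | WAI-SR |
| Testing completion | none | chart, yes/no |

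ATGT and DCS are also taken twice, but are not named as Aim 4 outcomes.

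**3. Chance that the baseline score is selected**

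Inputs: n = 220 (Statistical analysis section); a two-sided 5% screen (assumed); c = correlation of the baseline score with one aspect (assumed); clustering ignored. By Fisher's z, the chance is approximately Φ(atanh(c)·√217 − 1.96). For c = 0.10: 0.1003 × 14.73 = 1.478, and Φ(1.478 − 1.96) = 0.315.

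| c | 0 | 0.10 | 0.15 | 0.20 |
|---|---|---|---|---|
| selected through one aspect | 5% | 32% | 61% | 85% |

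Screened against its own outcome, the same score would be selected in more than 99% of cases once the baseline-post correlation ρ is 0.3 or higher. Across 23 independent aspects with no true correlation (15 ratings plus 8 linguistic patterns), selection by chance alone is 1 − 0.95²³ = 69%. Entry is therefore often likely, but for reasons unrelated to the outcome.

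**4. False-positive rate for an aspect with no effect**

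Simulation: n = 220, one aspect, c = 0.10 to 0.20, ρ = 0.5 to 0.75, nominal 5%, no clustering, 10,000 runs per setting.

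| Model | Rate |
|---|---|
| Baseline never included | 0.11 to 0.61 |
| Step 1 screen as written | 0.055 to 0.064 |
| Baseline always included | 0.044 to 0.052 |

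At c = 0 the written screen gives 0.034 to 0.042, slightly below nominal. The screen controls confounding reasonably well because a score that confounds an aspect must correlate with that aspect, which is what Step 1 tests.

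**5. Precision when baseline is included**

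Residual variance falls to 1 − ρ², so 220 patients are worth 220/(1 − ρ²). Power is for a standardized aspect effect b = 0.15 (assumed), using Φ(b√220/√(1 − b² − ρ²) − 1.96). With baseline left out, power is Φ(2.250 − 1.96) = 0.61.

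| ρ (assumed) | Residual variance | Equivalent n | Power |
|---|---|---|---|
| 0.3 | 0.91 | 242 | 0.66 |
| 0.5 | 0.75 | 293 | 0.74 |
| 0.6 | 0.64 | 344 | 0.81 |
| 0.75 | 0.44 | 503 | 0.93 |

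The upper value of 0.75 is the test-retest reliability quoted for the trust scale and serves only as an illustrative ceiling. These gains are relative to a model without baseline. Where the screen happens to admit the score, the gain is already made.

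**The case against.** The strongest reply is that every baseline survey factor is already a candidate covariate, and that screening over all aspects will often admit the baseline score. This stands. It would be wrong to say that the outcomes are analyzed on the post-encounter score alone. Nor is everything measured after the encounter outside Step 1: the provider's alliance rating and the provider's report of the testing decision are in the provider post-encounter survey, though only as candidate covariates.

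A second reply is that a condensed article may leave covariate lists to the full plan. That would excuse a missing list. Here the algorithm is given step by step, and its purpose and its computation disagree.

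Three stronger readings are tempting, and the documents do not support them.

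- **Badly inflated false positives.** A reader might infer this from the missing baseline term. The high rates in the working belong to a model that never adjusts. When the score is screened out, its sample correlation with the aspect is small, and so is the spurious association.
- **Distorted racial-disparity conclusions.** The article gives no figures on baseline trust or empowerment by race, and the written screen leaves little confounding to carry such a distortion.
- **A same-scale baseline for all five outcomes.** This is true of empowerment and, in reworded form, of trust. Baseline satisfaction concerns the healthcare system on a different instrument and is not a baseline for the GCSS. Alliance and testing completion have none.

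**Conclusion.** The point holds in a limited form and should be fixed. Step 1 of Aim 4 contradicts its own purpose: it omits the patient-reported outcomes and testing completion, and Steps 2 and 3 inherit the resulting covariate set. For empowerment and trust, a probably strong predictor that is already to be collected may be in or out of the model for reasons unrelated to how well it predicts the outcome.

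The harm is mainly lost precision and a data-dependent model. Where baseline would otherwise be left out, including it lowers residual variance by 9 to 56%. That range rests on an assumed baseline-post correlation of 0.3 to 0.75, and the lower part may be more realistic for trust because the baseline item is an expectation. Residual confounding is small, at about 0.05 to 0.065 against a nominal 0.05. All figures ignore clustering within providers and the Bonferroni correction.

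**What to change.** 1. Reword Aim 4 Step 1 so that candidate covariates are correlated with the patient-centered outcomes, including the patient post-encounter scores and testing completion.
2. Prespecify baseline GOS in the empowerment model and the baseline expected-trust score in the provider-specific trust model, in both the Step 2 partial correlations and the Step 3 regressions, whatever the screen shows.
3. Let these two terms be outcome-specific, as an exception to the rule that all regressions share one covariate set. The rest of the shared set can stay.
4. If ATGT or DCS is analyzed as an outcome, include its own baseline score in the same way.

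The cost is a change of wording and one patient-level covariate per affected model. No new data are needed, because the planned patient baseline survey already contains these scales.
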